# Intermittent theta burst stimulation vs. high-frequency repetitive transcranial magnetic stimulation for post-stroke cognitive impairment: Protocol of a pilot randomized controlled double-blind trial

**DOI:** 10.3389/fnins.2023.1121043

**Published:** 2023-03-30

**Keywords:** post-stroke cognitive impairment (PSCI), high-frequency repetitive transcranial magnetic stimulation (HF-rTMS), intermittent theta burst stimulation (iTBS), electroencephalography, randomized controlled trial

## Abstract

**Introduction:**

Intermittent theta burst stimulation (iTBS), a novel mode of transcranial magnetic stimulation (TMS), has curative effects on patients with post-stroke cognitive impairment (PSCI). However, whether iTBS will be more applicable in clinical use than conventional high-frequency repetitive transcranial magnetic stimulation (rTMS) is unknown. Our study aims to compare the difference in effect between iTBS and rTMS in treating PSCI based on a randomized controlled trial, as well as to determine its safety and tolerability, and to further explore the underlying neural mechanism.

**Methods:**

The study protocol is designed as a single-center, double-blind, randomized controlled trial. Forty patients with PSCI will be randomly assigned to two different TMS groups, one with iTBS and the other with 5 Hz rTMS. Neuropsychological evaluation, activities of daily living, and resting electroencephalography will be conducted before treatment, immediately post-treatment, and 1 month after iTBS/rTMS stimulation. The primary outcome is the change in the Montreal Cognitive Assessment Beijing Version (MoCA-BJ) score from baseline to the end of the intervention (D11). The secondary outcomes comprise changes in resting electroencephalogram (EEG) indexes from baseline to the end of the intervention (D11) as well as the Auditory Verbal Learning Test, the symbol digit modality test, the Digital Span Test findings, and the MoCA-BJ scores from baseline to endpoint (W6).

**Discussion:**

In this study, the effects of iTBS and rTMS will be evaluated using cognitive function scales in patients with PSCI as well as data from resting EEG, which allows for an in-depth exploration of underlying neural oscillations. In the future, these results may contribute to the application of iTBS for cognitive rehabilitation of patients with PSCI.

## 1. Introduction

Post-stroke cognitive impairment (PSCI), one of the most common complications of stroke (Zlokovic et al., 2020), refers to a variety of symptoms ranging from mild cognitive impairment to dementia. Approximately 20–70% of stroke survivors suffer cognitive impairment within 6 months of stroke (Liao et al., 2021; Merriman et al., 2021). Due to impaired attention, memory, language, and visuospatial functions, PSCI impedes recovery from stroke-related sequelae, including sensory impairment, motor dysfunction, and limitations in daily activities (Viktorisson et al., 2021). Currently, evidence-based treatment guidelines for PSCI are lacking, due to the limited pharmacological (donepezil, galantamine, and memantine) and non-pharmacological therapies (cognitive training and physical interventions) (Mijajloviæ et al., 2017). Hence, the identification of optimal and effective treatment is crucial. Recent studies have shown that neuromodulation techniques help improve cognitive impairment through neuroplasticity (Paolucci et al., 1996; Cicerone et al., 2011; Paolucci, 2013; Di Lazzaro et al., 2021), similar to repetitive transcranial magnetic stimulation (rTMS), which has been proven by several meta-analyses to have promising and positive effects (Lefaucheur et al., 2014, 2020; Hara et al., 2021; Liu et al., 2021; Zhang et al., 2021). Intermittent Theta Burst Stimulation (iTBS) is a novel neuromodulation technique with a unique advantage in treatment time compared to rTMS (Huang et al., 2005) and a reported better facilitation effect on modulating cortical excitability in brain regions (Blumberger et al., 2018; Kaster et al., 2019; Si et al., 2019). ITBS is effective and safe for treating depression, autism, and Parkinson’s disease in patients with mild cognitive impairment (Trung et al., 2019). However, evidence for iTBS treatment for patients with PSCI is limited. Some studies on PSCI have demonstrated that iTBS can improve patients’ overall cognitive function (Tsai et al., 2020; Li et al., 2022), specifically memory function (Tsai et al., 2020). However, the therapeutic mechanism of iTBS remains unclear, in the absence of sufficient neuroimaging assessments and long-term follow-up (Tsai et al., 2020; Li et al., 2022). In addition, there is inadequate evidence to suggest that iTBS is equally or more effective than traditional rTMS in terms of the treatment outcome. Therefore, we are conducting a randomized, double-blind controlled trial using neurobehavioral assessments combined with a neurobehavioral method, electroencephalogram (EEG), to compare the difference in effect between iTBS and rTMS in treating PSCI, as well as to explore neuroelectrophysiological changes. We hope to provide a theoretical basis for PSCI treatment. The protocol for this trial has been prepared according to the recommendations for interventional trials (SPIRIT) 2013 guidelines (Chan et al., 2013).

## 2. Methods and analysis

### 2.1. Patients

#### 2.1.1. Study setting

This study will be conducted at Zhujiang Hospital, Southern Medical University (Guangzhou, China). Forty inpatients with PSCI in the rehabilitation medicine ward will be included between October 2022 and December 2023.

#### 2.1.2. Eligibility criteria

Researchers will screen patients based on the inclusion and exclusion criteria. Once participants are confirmed as eligible, they will sign an informed consent form. To maintain safety criteria, we will not enroll patients who are intolerant to TMS. Women who are pregnant, breastfeeding, or intend to have children in the near future will not be eligible for enrolment. In addition, we will not enroll patients who have participated in other clinical trials or have a history of epilepsy. If a patient who has had TMS treatment has not received TMS treatment in more than 3 months, we may consider enrolling them. Finally, by conducting a preliminary exploratory study to compare clinical efficacy between rTMS and iTBS therapy on patients with PSCI, we aim to analyze data within and between the two hemispheres (the healthy and the affected sides) for the dynamic changes of oscillations to mine additional information. In light of the above statistical analysis, we decide to exclude patients with bilateral lesions from this study.

##### 2.1.2.1. Inclusion criteria

• Age 18 to 80 years;

• Stroke patients meeting the diagnostic criteria established at the Fourth National Cerebrovascular Disease Academic Conference in 1995;

• Imaging evidence of stroke confirmed by computed tomography (CT) or magnetic resonance imaging (MRI);

• Montreal Cognitive Assessment Scale (MoCA) score ≤24;

• Cognitive impairment should occur within 12 months of the vascular event and last for at least 3 months;

• First-ever stroke;

• Right-handed;

• Normal cognitive function before stroke;

• No severe aphasia (screened by the Chinese Aphasia Battery) and capable of completing cognitive tests;

• Stable vital signs;

• Voluntary participation and signed informed consent (signed by the patient or another authorized representative).

##### 2.1.2.2. Exclusion criteria

• Complete damage to the left prefrontal cortex confirmed by CT/MRI;

• Bilateral brain lesions;

• Defect of the skull;

• Use of antidepressants or psychostimulants;

• Metal or cardiac pacemaker implants near the treatment site;

• Previous brain disorders such as brain tumors, brain trauma, and seizures;

• History of malignant trauma;

• Unstable vital signs or failure of vital organs;

• Any neuropsychiatric comorbidity or affective disorder that could affect the test results;

• Patients with dementia (Clinical Dementia Rating grade ≥0.5) who are unable to cooperate with the cognitive assessment and intervention described below.

#### 2.1.3. Participant timeline

The study will begin by screening the participants for eligibility. Once the patient’s eligibility has been confirmed, an informed consent form will be signed, and the patient will be randomly assigned to one of the two treatment groups. Clinical assessment and resting EEG measurements will be performed at baseline (D0), after 10 TMS treatments (D11), and at the 6-week follow-up (W6). It is possible that some participants will not be able to attend our hospital for their evaluation at W6. Therefore, we will present two situations. Participants who can return to the hospital will have their EEG data collected at W6, while those who are unable to return to the hospital will be evaluated door-to-door. A record will be made if a patient leaves the trial, is excluded, or withdraws at any point, along with the reasons. The visit schedule and study flowchart are presented in Table 1 and Figure 1.

**TABLE 1 T1:** Trial schedule.

	Trial schedule				
	**Enrollment**	**Allocation**	**Post-allocation**	**Close-out**	**Follow-up**
**Timepoint**	**-D1**	**0**	**D1–D10**	**D11**	**W6**

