### 2.3. Outcomes

Our primary outcome will be the Montreal Cognitive Assessment Beijing Version (MoCA-BJ) score from baseline to the end of the intervention (D11). Secondary outcomes will be resting EEG indexes, the Auditory Verbal Learning Test (AVLT), the symbol digit modality test (SDMT), the Digital Span Test (DST), and adverse events. Indexes of resting EEG include the absolute power and relative power of neural oscillations. Other outcomes include the Hamilton Depression Scale (HAMD) and Activities of Daily Living (ADL). All clinical assessments will be performed thrice: pre-treatment (baseline), post-last treatment, and at the 1-month follow-up. An experienced physician will conduct all cognitive assessments throughout the study and will be blinded to the participants’ group assignment and trial phases. The resting EEG will be conducted at baseline and at the end of TMS treatment.

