#### 2.3.2. Resting EEG measurements

A resting EEG is a graphical representation of the spontaneous electrical activity of a population of brain cells. It is obtained by magnifying and recording spontaneous biopotentials of the brain from the scalp using sophisticated electronic equipment (Höller and Nardone, 2021). EEG signals will be recorded using an EEG cap equipped with 64 Ag/AgCl electrodes, arranged according to the Extended International 10–20 electrode placement system (Tamburro et al., 2020). A 5-min EEG recording will be conducted with participants seated comfortably in a sound-insulated, dimly lit room with their eyes closed. All channels will be referenced online to the bilateral mastoid and amplified using an amplifier (Compumedics Neuroscan, Neuroscan 8050). Data will be sampled at 2,048 Hz, with impedances kept below 10 kΩ for all channels throughout data collection.

The acquired EEG signals will be analyzed offline using MATLAB2013b. Given previous evidence that oscillatory dynamics are affected by rTMS (Thut et al., 2011; Veniero et al., 2011; Chota et al., 2021) and are closely related to cognitive improvement (Klimesch et al., 1993; Richard Clark et al., 2004; Iliopoulos et al., 2020), we will analyze the power spectrum and functional connectivity of each oscillation within and between hemispheres, between groups, and pre- and post-treatment. Oscillation ratios, such as θ/α ratio, θ/γ ratio, and (α + β)/(θ + δ) ratio will be further analyzed (Coben et al., 1985; Moretti et al., 2013; Sato et al., 2022).

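### The article gives two resting-EEG schedules, with and without W6, and any W6 EEG would cover only participants able to return to hospital

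*Protocol article*

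**What the plan says.** Two places in the protocol article give three EEG recordings. The Abstract (Methods) states that "resting electroencephalography will be conducted before treatment, immediately post-treatment, and 1 month after iTBS/rTMS stimulation". Section 2.1.3 has the same three visits: "Clinical assessment and resting EEG measurements will be performed at baseline (D0), after 10 TMS treatments (D11), and at the 6-week follow-up (W6").

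Two places give two recordings. Section 2.3 states: "The resting EEG will be conducted at baseline and at the end of TMS treatment". In Table 1 the EEG row has crosses at time 0 and D11 only, while the row of clinical scales directly above it has a third cross at W6.

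Section 2.1.3 also says who would have a W6 recording. It warns: "It is possible that some participants will not be able to attend our hospital for their evaluation at W6". It then separates two situations. In the first, "Participants who can return to the hospital will have their EEG data collected at W6". In the second, which is a home visit, "those who are unable to return to the hospital will be evaluated door-to-door". No EEG is mentioned for the home visits.

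The only EEG endpoint with a declared window is the secondary outcome in the Abstract: "changes in resting electroencephalogram (EEG) indexes from baseline to the end of the intervention (D11"). Section 2.4 compares relative spectral energy between groups and over time by repeated-measures ANOVA, but does not say which time points enter.

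**The concern.** A site cannot follow both schedules, and section 2.1.3 refers the reader to the very table that it contradicts. This is a conflict in the current text, so it is not a detail left to a fuller document.

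The conflict matters for the analysis in two ways. First, if W6 EEG is recorded, it comes from a subset formed after randomisation by ability to return. If that ability is related to the EEG measure, the W6 values do not represent the randomised patients. Second, section 2.4 leaves open whether W6 belongs in the EEG model. Classical repeated-measures ANOVA needs every time point for each patient. If W6 were one of them, a patient without W6 EEG could also drop out of the D11 comparison, which the plan declares as a secondary outcome and which that patient had completed.

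**Working it through.** The plan states no figure for this point, so there is none to reproduce. The check sets the texts side by side and then sizes the two possible consequences under stated assumptions.

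**1. The schedules**

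| Place | Baseline | D11 | W6 / 1 month |
|---|---|---|---|
| Abstract, Methods | yes | yes | yes |
| 2.1.3 text | yes | yes | yes, if able to return |
| Table 1 | yes | yes | no |
| 2.3 | yes | yes | no |

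Visit labels do not explain the difference. W6 is day 42, and 42 − 11 = 31 days, so W6 and the 1-month follow-up are the same visit. The empty Table 1 cell is unlikely to be a text-extraction fault, because 2.3 says the same in prose.

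**2. Who could have a W6 EEG**

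Section 2.3.2 describes a 64-electrode cap, with "participants seated comfortably in a sound-insulated, dimly lit room with their eyes closed". A home recording under those conditions is unlikely, though the article does not rule it out. As 2.1.3 reads, W6 EEG comes only from returners.

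**3. Precision of the D11 comparison**

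Inputs: 40 patients, 20 per arm (section 2.1.4). Assumed: W6 enters the EEG ANOVA, the ANOVA uses complete cases, a share q does not return (equal in both arms), all 40 have D11 EEG, and the SD is unchanged.

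Ratio of standard errors = √(40 / [40(1 − q)])

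- q = 20%: √(40/32) = 1.118, an increase of about 12%.
- q = 40%: √(40/24) = 1.291, an increase of about 29%.

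Section 2.1.4 already allows for 20% loss (40 to 32), so the lower end is a number that the plan has accepted. Measured from 32, a fall to 24 gives √(32/24) = 1.155, about 15%.

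**4. Selection at W6**

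Assume that ability to return is a normal variable with correlation r to the W6 EEG measure, and that the top share p return. The returners' mean shifts by r·φ(t)/p SD, with t = z(1 − p). The article gives neither r nor p.

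| p returning | of 20 per arm | r = 0 | r = 0.3 | r = 0.5 |
|---|---|---|---|---|
| 90% | 18 | 0 | 0.058 | 0.097 |
| 80% | 16 | 0 | 0.105 | 0.175 |
| 60% | 12 | 0 | 0.193 | 0.322 |
| 50% | 10 | 0 | 0.239 | 0.399 |

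Between-arm bias is the difference between the two arms' shifts:

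- Equal return in both arms: 0.
- 90% against 70%: 0.091 SD (r = 0.3) to 0.151 SD (r = 0.5).
- 80% against 50%: 0.134 SD to 0.224 SD.

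These are shifts in the W6 level. Under complete-case analysis the same returners supply all three visits, so a stable difference in level cancels from within-patient time and group-by-time contrasts. Bias there would need return to be related to EEG change, which this model does not cover. The figures in steps 3 and 4 should therefore not be combined as if they described one analysis.

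**The case against.** The strongest case against is that the plan's EEG inference already stops at D11. The Abstract sets that window, 2.3 and Table 1 match it, no W6 EEG endpoint is declared, and a model with two time points satisfies 2.4. Handling of missing data is commonly left to an analysis plan, which is not shown. Section 2.1.3 also foresees non-return and separates the two situations. All of this limits the consequence. It does not remove the conflict, since the Abstract and 2.1.3 still schedule a third recording.

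A reader might infer that W6 EEG results are selected by recovery. The documents do not support that as fact. They give no reason for non-return. Patients are enrolled as ward inpatients, so distance from home after discharge is another possible reason. What can be said is that selection is by ability to return, which after stroke may be related to recovery. Nor can a bias in the direction of recovery be claimed, because the article names several power measures and ratios without saying which direction means improvement.

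A reader might also infer that the D11 EEG comparison will lose patients. That needs W6 in the model and complete-case deletion, and the article states neither.

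**Conclusion.** The contradiction is certain: two places against two. It should be resolved before the EEG data are analysed.

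The consequences are conditional. If W6 entered a complete-case ANOVA, the standard error of the declared D11 EEG comparison would rise by about 12% to 29% at 20% to 40% non-return, relative to all 40 patients. This loss would occur even if return had nothing to do with recovery. Selection bias in W6 EEG cannot be sized from the documents. It is zero if return is unrelated to the EEG measure, and in the simple model used here the between-arm bias is also zero if return is equal by arm.

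The point concerns a secondary outcome. The primary MoCA-BJ outcome at D11 is not affected.

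**What to change.** - Bring the Abstract, 2.1.3, 2.3 and Table 1 to one EEG schedule. Either direction is coherent: drop W6 EEG from the first two, or add it to the last two as an exploratory recording in returners.
- In 2.4, name baseline and D11 as the EEG time points. Compare arms on D11 EEG, adjusted for baseline, in all patients with D11 EEG. The baseline adjustment is a modelling recommendation; the conflict itself does not require it.
- If W6 EEG is kept, label it exploratory, keep it out of that model, and report by arm how many returned and why the others did not. The log in 2.1.3 records reasons for leaving, exclusion or withdrawal, and does not clearly cover a patient who stays in the trial but is seen at home.

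The cost is wording in the four places and in 2.4, plus a record of reasons for non-return. There would be no inferential W6 EEG result. Recruitment was planned from October 2022 and the article appeared in March 2023, so removing a W6 recording could also change conduct already under way. Keeping it as exploratory avoids that.

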**Enrolment**					
Eligibility screen	×				
Informed consent	×				
Allocation		×			
**Interventions**					
(rTMS)			×———×		
(iTBS)			×———×		
**Assessments**					
Demographics and clinical characteristics		×			
MoCA; AVLT; SDMT; DST; HAMD; ADL		×		×	×
Resting EEG		×		×	

DLPFC, dorsolateral prefrontal cortex; rTMS, repetitive transcranial magnetic stimulation; iTBS, intermittent theta burst transcranial magnetic stimulation; MoCA, Montreal cognitive assessment; AVLT, auditory verbal learning test; SDMT, symbol digit modalities test; DST, digital span test, HAMD: Hamilton depression scale; ADL, activities of daily living; EEG, electroencephalography.

**FIGURE 1 F1:**
[figure not shown]
Design and flow of participants through the study.

#### 2.1.4. Sample size

This will be an exploratory study. The required sample size for this study was estimated using GPower software (version 3.1.9.7) (Faul et al., 2007). Repeated measures analysis of variance (ANOVA) will be used for statistical analysis, with group and time as affecting factors. Accordingly, the *F*-test (repeated-measures ANOVA, between factors) was chosen, with a power of 85%, an alpha value of 0.05, and an effect size of 0.25 (Cunningham and Mccrum-Gardner, 2007). The predicted minimum sample size was 32 (two groups) considering a 20% loss to follow-up. Therefore, we set the sample size at 40 patients in total, with 20 patients in each group.

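### The sample size of 32 does not follow from the between-factors test that section 2.1.4 names; it matches a different repeated-measures test, with inputs the section leaves unstated

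*Protocol article*

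**What the plan says.** The protocol article, section 2.1.4 (Sample size), says the number was "estimated using GPower software (version 3.1.9.7"). It plans a repeated-measures ANOVA with group and time as factors, and names the F-test used for sizing: "repeated-measures ANOVA, between factors) was chosen, with a power of 85%, an alpha value of 0.05, and an effect size of 0.25". The result is given as "The predicted minimum sample size was 32 (two groups) considering a 20% loss to follow-up", after which "we set the sample size at 40 patients in total, with 20 patients in each group".

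The section gives neither the number of repeated measurements nor the correlation between them. Section 2.3 (Outcomes) supplies the first: "All clinical assessments will be performed thrice: pre-treatment (baseline), post-last treatment, and at the 1-month follow-up". Table 1 shows the same schedule for the clinical scales. The primary outcome, MoCA-BJ from baseline to D11, uses two of the three visits. Section 2.4 analyses the scales by repeated-measures ANOVA for differences between time points and groups.

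**The concern.** In a two-group repeated-measures design, the between-factors test compares the arms on each patient's average over all visits. The group-by-time interaction compares them on change over time. The two respond to correlation in opposite ways: a higher correlation makes the first less powerful and the second more powerful. With a modest f of 0.25, a total of 32 looks far too small for the first test.

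This calculation is the only quantitative justification for 40 patients. If the test and the number do not belong together, a reader cannot tell which comparison is meant to have 85% power, or for what effect. That matters because the Discussion says the trial will examine whether iTBS is non-inferior or superior to rTMS. A power figure attached to the wrong comparison could colour the reading of a null result.

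**Working it through.** **Inputs.** From section 2.1.4: k = 2 equal groups, f = 0.25 (read as Cohen's f), alpha = 0.05, power 85%, loss 20%. From section 2.3: m = 3 measurements. Not stated anywhere: the correlation ρ between measurements, so a range is shown. Sphericity (ε = 1) is assumed for the within-patient tests. Power comes from the noncentral F distribution, and N is searched in steps of 2.

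**Step 1: where 32 comes from.** For the group-by-time interaction (and the within-factors test, whose formula is the same here):

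λ = f²·N·m / (1 − ρ), with df = m − 1 and (N − 2)(m − 1).

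With m = 3 and ρ = 0.5:
- N = 30: λ = 0.0625 × 30 × 3 / 0.5 = 11.25, df 2 and 56, power 84.1%.
- N = 32: λ = 0.0625 × 32 × 3 / 0.5 = 12.0, df 2 and 60, power 86.6%.

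So 32 is the smallest even N that reaches 85%, and 32 / 0.8 = 40. Both figures in the protocol reproduce.

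**Step 2: the test the protocol names.** For between factors:

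λ = f²·N·m / (1 + (m − 1)ρ), with df = 1 and N − 2.

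With m = 3 and ρ = 0.5:
- N = 32: λ = 6 / 2 = 3.0, df 1 and 30, power 38.9%.
- N = 40: λ = 7.5 / 2 = 3.75, df 1 and 38, power 47.1%.
- N = 98: λ = 18.375 / 2 = 9.19, df 1 and 96, power 85.1%. N = 96 falls just short at 84.4%.

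Over the range of correlations, m = 3:

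| ρ | N for 85% | Power at 32 | Power at 40 |
|---|---|---|---|
| 0 | 50 | 66% | 76% |
| 0.3 | 80 | 47% | 56% |
| 0.5 | 98 | 39% | 47% |
| 0.7 | 118 | 33% | 41% |
| 0.9 | 138 | 29% | 36% |

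With m = 2 the requirement runs from 74 (ρ = 0) to 140 (ρ = 0.9). Reaching 32 with three visits takes a correlation of about −0.2, which is implausible for repeated scores on one patient.

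**Step 3: the interaction on the two primary visits.** With m = 2 and ρ = 0.5:
- N = 32: λ = 0.0625 × 32 × 2 / 0.5 = 8.0, df 1 and 30, power 78%.
- N = 40: λ = 10.0, df 1 and 38, power 87%.
- The smallest N for 85% is 38.

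At ρ = 0.3 the power is 64% / 74% at 32 / 40 completers, and at ρ = 0.7 it is 94% / 98%.

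**Step 4: what f = 0.25 means for the interaction.** Here f is the root mean square of the interaction effects divided by the SD of a single score. The implied between-arm difference in change depends on the mean pattern:
- two visits: 4f = 1.00 SD;
- three visits, difference present at D11 and unchanged at follow-up (0, d, d): d = f√18 = 1.06 SD;
- three visits, difference growing in equal steps (0, d/2, d): d = f√24 = 1.22 SD.

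**The case against.** The strongest reply is that this is a mislabelled software option. Section 2.1.4 lists group and time as factors and section 2.4 compares time points and groups, so an interaction test fits the design. The number 32 reproduces under it, and 20% loss then gives 40. This largely stands, and it limits what can be claimed.

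A reader might infer that the trial really needs 98 patients and has under 50% power. The document does not support that. Both figures require ρ = 0.5, which the protocol does not state. At ρ = 0.3 the named test has 56% power with 40 patients. For the interaction, which may be what was actually sized, three measurements at ρ = 0.5 give about 87% with 32.

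The two-visit result also cuts both ways. The 78% applies the whole 20% loss by D11. Section 2.1.3 expects attendance difficulty at W6, and the patients are inpatients treated on ten consecutive days. No separate loss rate for D11 is given, so 78% (32 completers) and 87% (40 completers) must both be shown.

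It is also fair to say that the protocol never calls 0.25 moderate, that the trial is presented as a pilot and exploratory, and that small size is listed as a limitation. These labels make it less likely that a null result would be over-read. They do not reconcile a stated test with a number it does not produce. Nor is this a detail that can be left to a separate analysis plan, because the inputs and the result are both printed and disagree.

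Finally, the wording about 32 and the 20% loss is ambiguous. If 32 already included the loss, about 26 would be evaluable (32 × 0.8 = 25.6), and the named test would have 32% power at ρ = 0.5, so that reading widens the gap.

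**Conclusion.** The point holds as a mismatch between the named test and the reported sample size. For every non-negative correlation with three visits, the between-factors test needs at least 50 patients, and its power is at most 66% with 32 and 76% with 40. That conclusion rests only on reading 0.25 as Cohen's f and on the three visits in section 2.3. Any single figure inside the range depends on an assumed correlation.

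The likeliest source of 32 is the within-factors or interaction option with m = 3, ρ = 0.5 and sphericity. This is an inference from an exact match, not something the protocol states. On that reading the trial is not shown to be underpowered for the interaction. What the reader is not told is that f = 0.25 then stands for a difference in change of roughly 1 SD between two active stimulation protocols.

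**What to change.** Keep 40 patients and rewrite the paragraph in section 2.1.4 in one of two ways:

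1. Name the group-by-time interaction as the sized test. State the number of measurements (3), the correlation (0.5, if that was used) and the sphericity assumption. Say what f = 0.25 means as a between-arm difference in change: about 1 SD, with the assumed mean pattern given.
2. Keep the between-factors test and replace the 85% with its actual power over a range of correlations, as in the table above.

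Either way, say plainly that 32 is the number before the 20% allowance.

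An optional addition is the detectable difference for the primary comparison at D11. With 16 completers per arm and 85% power, a baseline-adjusted comparison detects about 0.95 SD at correlation 0.5 and 0.78 SD at 0.7. This is not needed to cure the mismatch and does not oblige the sponsor to replace the planned ANOVA.

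The cost is one reworded paragraph and no extra patients. The stated power, or the effect the trial can detect, will look less favourable than it does now.
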